### 9.2.3 6-Minute Walk

The 6MW will be performed in accordance with standard practice. Briefly, site personnel will discuss the 6MW test with each patient, and will then allow each patient to complete one practice walk before the Screening 6MW. The practice walk is not required if the patient has completed a documented (in the medical record) 6MW within 3 months of the Screening 6MW. The subject will be encouraged to walk as fast as possible during the preliminary instructions. However, once the walk begins the technician may not provide additional encouragement. Distance walked, Borg dyspnea index, NYHA functional class, and oxygen saturation will be determined (see Appendix D). Once the practice walk is completed, the site personnel will conduct the actual Screening 6MW  $\geq 2$  hours after the practice walk. Upon enrollment into the MIT, at least one additional 6MW test will be completed with each patient prior to Randomization. No additional practice walks will be conducted during the MIT.

The 6MW test performed at baseline must satisfy the following requirements:

- The 6MW test #2 distance should be within 15% of 6MW test #1 distance or a third test is required (6MW test #3). If screening and baseline 6MWs take place on the same day, the 6MW test #1 and 6MW test #2 must be done at least 2 hours apart.
- The 6MW test #3 distance should be within 15% of 6MW test #2 distance or the subject cannot be included in the study. The 6MW test #2 and #3 must be done at least 2 hours apart.
- For the subjects treated with long-term oxygen therapy, the walk test should be performed without supplemental oxygen. If interruption of the oxygen supply is deemed as unsafe and it is required during the baseline 6MW, follow-up 6MWs must be conducted at the same flow rate.

During follow-up visits 6MW tests should be performed on peak study medication dose i.e. 1-2 hours after study medication intake.

### 9.2.4 Clinical Outcome Adjudication

A subset of clinical outcomes that occur during the randomized, double-blind phase will be adjudicated by a blinded panel of experts. Adjudicated outcomes include: ACS, right heart failure, and clinical deterioration of PH.

In order to determine clinical deterioration of PH, the adjudication panel will consider, at a minimum, the following:

- 20% decrease in six-minute walk distance, on two successive evaluations taken at least 2 weeks apart while not in VOC, plus deterioration in NYHA/WHO functional class
- Initiation of additional PH specific therapy, that is, prostanoid analogue, endothelin receptor antagonist or PDE 5 inhibitor

### 9.2.5 Candidate Gene Analysis

The intention of collecting DNA samples in this population is to perform extensive genome wide genetic analysis followed by segments of regions associated with pulmonary hypertension. When available in the next five years, whole genome sequence DNA on this population samples will be performed. Specifically, automated DNA sequencing of candidate genes, novel PCR based assays, and “chip” based high-throughput SNP detection platforms will be conducted at the NHLBI through the Division of Intramural Research or through collaboration with other Institutes.

For the purpose of the genetic study design cases will be recruited as specified in the protocol (individuals meeting criteria for a diagnosis of SCD and PH). Individuals with SCD not meeting criteria for PH will serve as a first control group, and will be used to identify susceptibility determinants for PH as a whole.

Candidate genes for detailed examination will be selected from a list of cytokines, adhesion molecules, and genes identified by microarray expression analysis that are potentially involved in the pathogenesis of SCD pulmonary hypertension. Specific candidate genes to be studied are listed in Appendix E.

## 9.3 Scientific and Safety Evaluations

### 9.3.1 Biomarker Analyses

All subjects will provide blood for the biomarkers studies. Approximately 30 mL of blood will be needed for the set of assays on a given day (see Table 5). The baseline sample (Day 1) will be drawn at study entry before study drug is administered. Samples will be processed and shipped from participating sites to the NHLBI sample repository, as well as shipped to the NHLBI central laboratory for evaluation of the pro Brain Natriuretic Peptide levels.

**Table 5. Investigational Laboratory Studies (Biomarkers)**

| Biomarker Assessed                      | Screening | Baseline | Week 6 | Week 10 | Week 16 |
|-----------------------------------------|-----------|----------|--------|---------|---------|
| NT pro Brain Natriuretic Peptide levels | X         | X        | X      | X       | X       |
| Plasma for storage                      | X         | X        | X      | X       | X       |

### 9.3.2 Clinical Laboratory Tests

Clinical laboratory tests (including the pregnancy test, if applicable) will be performed on blood samples collected at screening and all clinic visits for the Main Interventional Trial. Urinalysis laboratory tests will be performed on urine samples collected at screening and all clinic visits for the MIT as well. The following laboratory tests will be performed:

- Liver function tests (AST, ALT, albumin, total protein, total bilirubin, alkaline phosphatase)
- Renal function tests (potassium, sodium, chloride, bicarbonate, blood urea nitrogen (BUN), and creatinine)
- Mineral panel tests (magnesium, phosphate, calcium)
- CBC (Hemoglobin, hematocrit, RBC, MCHC, mean cell volume (MCV), reticulocyte counts, white blood cell (WBC) count, platelet count, and ANC)
- LDH
- INR values for subjects who are on vitamin K antagonists (e.g. warfarin)
- Activated Partial Thromboplastin Time (aPTT) for subjects who are on therapeutic doses of unfractionated heparin

### **9.3.3 Physical Examination and Vital Signs**

A physical examination and set of vital signs will be assessed at each clinic visit. Vital sign measurements include weight, diastolic and systolic blood pressure, heart rate, and temperature.

To determine whether the subject's blood pressure qualifies him/her for the MIT, have the subject rest for at least 5 minutes prior to the assessment. Up to 3 blood pressures may be taken. Once an assessment qualifies on BOTH the systolic and diastolic, no further assessments are needed, and the subject qualifies for the study per exclusion criterion #12. The intent is to exclude patients who have uncontrolled systemic hypertension, rather than to exclude patients in a temporary/transitory state with a one time measurement out of normal range (e.g., "white coat hypertension"). Therefore, if the clinician believes, based on experience with the subject, that the blood pressure assessment is not reflective of the subject's actual level of systemic blood pressure, the assessment may be repeated.

### **9.3.4 Medical History**

At screening, the subject's medical history will be recorded including: previous treatment for SCD, previous ACS events, previous strokes, pain crises frequency and usual management, history of priapism, previous transfusions and reactions to transfusions and to medications.

The subject's interim medical history will be recorded at baseline and every clinic visit of the MIT, focusing on emergency department (ED) visits, day clinic visits, hospitalizations, self-medicated crises, and analgesic usage (see Appendix B for sample data collection tool).

## **10 DATA MANAGEMENT**

### **10.1 Source Documentation**

All clinical data entered into the electronic Case Report Form (eCRF) must be supported by signed source documentation maintained at the clinical site. Specifics of source documentation maintenance will be detailed in the Walk-PHaSST Manual of Operations.

### **10.2 Data Management**

The site study coordinator will enter clinical data into the CRF for each subject via the secure internet access, Rho Electronic Data Capture System (RhoEDC™). A CRF completion guide will be available online to assist in correct CRF completion. On all other study documents, subjects will be identified by a subject number assigned at enrollment, and will not be identified by name.

Using this system, clinical site personnel will use an internet browser (Internet Explorer or similar) to key data into an electronic CRF. The screens will be accessible via the Walk-PHaSST website and require site-specific user ID/password privileges. Univariate data validation tests will be performed as the data are keyed; most implausible data values will be resolved immediately.

Data will not be stored on the site's computer. At the end of each "page," data will be submitted to DCC's secure web server using SSL (128 byte public key encryption methodology) and stored in the study's "operational database." (The database used for capturing, validating, updating, and storing the data is called an "operational database"). The database will be backed up nightly; backup tapes will be saved in a secure, off-site location. Authorized site personnel may log in to the system, review and correct previously entered data, key additional data, or lock records to prevent further inadvertent modifications at any time.

### **10.3 Staff Training**

Prior to the onset of enrollment, clinical study coordinators and data coordinators will be centrally trained to ensure adherence to the protocol and assure the highest possible data quality. Training will be led by a combination of investigators and other staff from the clinical sites, the DCC, and NHLBI. Training presentations will address informed consent procedures, study operations and protocol requirements, data collection procedures, maintenance of source documentation, CRF completion and review, routine reporting requirements, data entry and management, and NHLBI policies and procedures. As needed and as time allows, in-person training will be provided by DCC staff as part of periodic site visits.

### **10.4 Data Monitoring**

After training, site study coordinators will have the responsibility of monitoring CRFs and source documents for accuracy, protocol compliance, subject safety, and adherence to guidelines outlined in the Manual of Operations.

As referenced above, sites will be visited by a DCC CRA or qualified designee. At each site visit, recruitment guidelines and study eligibility criteria will be reviewed. As the study progresses, completed data forms may be reviewed during site visits and compared to source documentation (medical or site records) to confirm accuracy.

## **11 STATISTICAL METHODS**

### **11.1 Analysis Populations**

This study is designed to enroll sickle cell disease subjects diagnosed with PH.

*Intent-to-Treat (ITT) / Safety population (SAF):* All randomized subjects will be included in the ITT/SAF population. Subjects in the ITT/SAF population will be classified according to the treatment group to which they were randomized, regardless of what study drug they received.

*Per-Protocol (PP) population:* The PP population consists of all subjects from the ITT/SAF population who had no major protocol violations and who were followed until discharge from the study.

The primary efficacy analysis will be an intention-to-treat analysis. Secondary analyses of efficacy and safety will be performed on the ITT/SAF population, and many of the secondary efficacy analyses will be repeated on the PP population.

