- Emergency department visits, outpatient/day hospital visits and hospital admissions for sickle cell disease and those for complications of PH will be recorded
- Six-minute walk (with assessment of Borg dyspnea index, and NYHA/WHO functional class) 1-2 hours after taking the morning dose of study drug
- Echocardiogram with assessment of TRV LV and RV function 1-2 hours after taking the morning dose of study drug. All echocardiograms should be performed at least one hour after 6MW test. EXCEPTION NOTE: Echocardiogram will not be assessed at week  $10 \pm 1$
- Study drug compliance and daily pain assessment using the BPI --evaluated by subject for one week between each follow-up visit

End of the double-blind phase visit (week  $16 \pm 1$ ) will also include:

- In subjects with an initial study entry TRV  $\geq 3.0$  m/s a second right heart catheterization
- Quality of life assessment using SF-36 Quality of Life form (ages 14-adult) or Peds-QL (ages 12-13)

In subjects with TRV  $\geq 3.0$  m/s clinically indicated studies (according to accepted guidelines) for the work-up of subjects with pulmonary hypertension (PH) can be ordered at the discretion of treating clinicians. These studies could include:

- Collagen vascular screening tests (e.g., ANA, anti-centromere antibodies, anti SCL-70, antiphospholipid antibodies)
- Ventilation perfusion scan
- Chest X-ray (required for all MIT subjects at baseline), CT of chest
- Overnight pulse oximetry
- Spirometry with bronchodilation

- Lung volume
- Diffusing capacity for CO

Efficacy assessments will be done at peak dose (i.e., study medication should be taken 1-2 hours before measurements) when subjects are in a steady state.

A subset of clinical outcomes will be adjudicated by a blinded panel of experts. Adjudicated outcomes include: ACS, right heart failure, and clinical worsening.

Records of study drug used, dosages administered, and intervals between visits are kept during the study. Study drug accountability is performed on an ongoing basis by the study personnel and checked by the clinical research associate (CRA) during site visits and at the completion of the study. Subjects are asked to return all unused study drug at each visit.

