### **8.1 Packaging, Labeling, Blinding, Storage, and Return of Study Drug**

Pfizer will provide oral Revatio™ (sildenafil citrate) and matching Placebo (“Pfizer Product”) from multiple commercial batches, with differing expiration dates. Sildenafil citrate is a white to off-white crystalline powder with a solubility of 3.5 mg/mL in water and a molecular weight of 666.7. No additional dilution is required prior to administration. The product should be stored at controlled room temperature, 15° to 30°C (59°- 86° F). The study drug is stable through the date stamped on the product label and is administered orally.

All study drug (active and placebo) will be prepared by the central pharmacist at the Program Support Center, HHS Supply Service Center, [name], and shipped to participating sites’ pharmacies for dispensing. Study drug will be available in capsule formulation (over-encapsulated tablets). Placebo and active study drug capsules will

appear identical. The drug supply for the randomized double-blind phase will be packaged to allow the local site pharmacists to remain blinded to treatment group. Upon randomization of each subject, the Rho*RAND* system will send a randomization notification to the local pharmacist that provides the identification number of the bottle(s) (or kit) of study medication to be assigned/dispensed to that subject.

All unused study drug will be returned to the local pharmacy for disposal according to their standard operating procedures.

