## **8.2 Subject Compliance**

Good subject compliance/adherence will be critical to the success of the study and will therefore be monitored in multiple ways. Subjects will be required to return their bottles of sildenafil or placebo at every scheduled clinic visit in order to receive their new supply of “treatment.” Each site will count the number of pills returned and compare to the expected number of pills returned in order to calculate percent compliance. In addition, subjects will be instructed to maintain a study drug log for one week in-between each visit during the double-blind phase. They will record if and when they took their daily doses of study medication. Subjects whose diary or pill count suggest <75% compliance will be counseled.

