### **11.3 Safety Analyses**

All safety analyses will be performed using the ITT/SAF population. Safety variables will include laboratory variables and adverse event information. Specific endpoints that will be examined include:

- Incidence of AEs between baseline and Week 16
- Incidence of SAEs between baseline and Week 16
- Mortality incidence

The primary safety outcomes for the MIT will be all AEs; the subset of AEs defined as SAEs; and mortality. Treatment emergent AEs (those that begin or worsen after start of study drug), drug-related AEs, SAEs, and drug-related SAEs (as determined by the investigator) will be categorized by body system and MedDRA (Version 6.0 or later) preferred term.

The assessment of safety data will be based mainly on the tabulation of AEs, by TRV stratum and treatment arm. Additionally, AEs will be tabulated by severity and relationship to drug. Serious AEs will be described in detail. Comparisons across treatment groups, stratifying on TRV stratum will be made using a Cochran-Mantel-Haenszel chi-square test (or Fisher's Exact test as appropriate) on any AEs that occur in more than 10% of the subjects.

Additionally, continuous blood chemistry and hematology laboratory measurements will be categorized as normal/abnormal and summarized using shift tables, which describe changes in the values across visits.

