### 11.5.3 Multiple Comparisons and Multiplicity

The primary formal hypothesis test will be conducted using an alpha on a two-sided test of 0.05. Because only a single hypothesis test will be tested and other reported p-values will be considered descriptive, no adjustment for multiple comparisons will be made. Informal hypothesis tests conducted as a part of secondary analyses will all be two-sided tests, and the p-values from these tests will be presented as descriptive measures of strength of evidence. These descriptive p-values will be presented for differences between treatment groups in summary tables for secondary exploratory analyses.

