### **13.8.1 Reporting of All Serious Adverse Events to the DSMB**

Three months after the first subject is enrolled in the study, and at the end of each 3 month period thereafter, if any SAEs (expected or unexpected) have been reported in the study during the preceding 3 months, the DCC will:

- Use the current version of the MedDRA dictionary to code all AEs (serious or not) that have been recorded on study AE forms.
- Make a “snapshot” copy of the adverse events data, including MedDRA codes.
- Create frequency tables of treatment x occurrence (yes or no, since inception of the study) of all subjects. One table will be created for each highest-level MedDRA term for which SAEs have been reported. The counting units are subjects, not events.
- Compute Fisher’s Exact Test (FET) statistic to test the alternative hypothesis that occurrence of SAEs is not independent of treatment group. The FET p-value is not adjusted for multiplicity.
- If the FET p-value is less than the critical value shown in Table 12 and the active treatment group has a higher AE rate, the DCC will conduct further statistical analyses as indicated by the circumstances and report the results to the Chair of the DSMB subcommittee monitoring this study, the PI, and the NHLBI Project Officer.

The DCC will not file a report of all SAEs if none of the FET p-values is less than the critical value shown in Table 12 or if the relative risk is less than 1.

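### Safety is analysed as randomised whatever drug was taken, so any sildenafil harm in a placebo-randomised subject given sildenafil would be counted under placebo: a small, contingent bias that is cheap to remove

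*Protocol*

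**What the plan says.** Section 11.1 defines a single combined ITT/Safety population of all randomised subjects, "classified according to the treatment group to which they were randomized, regardless of what study drug they received". Section 11.3 leaves no exception: "All safety analyses will be performed using the ITT/SAF population". The same section rests the safety assessment mainly on adverse event tables by TRV stratum and treatment arm. It limits between-arm tests to a stratified comparison "on any AEs that occur in more than 10% of the subjects".

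The protocol contains no as-received safety set. The per-protocol set in 11.1 does not fill the gap, because only efficacy analyses are repeated on it.

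On supply, section 8.1 says the randomisation system sends the blinded site pharmacist a notification that "provides the identification number of the bottle(s) (or kit) of study medication to be assigned/dispensed to that subject". Supply is renewed during treatment: "Subjects will be required to return their bottles of sildenafil or placebo at every scheduled clinic visit in order to receive their new supply" (section 8.2). The dose steps in section 4.4.2.4 last 6, 4 and 6 weeks. On records, that section states: "Records of study drug used, dosages administered, and intervals between visits are kept during the study".

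**The concern.** Labelling by assigned arm dilutes a treatment difference whenever the drug taken differs from the drug assigned. For efficacy the dilution is conservative. For safety it works the other way, because it makes a harm of the active drug look smaller.

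The protocol fixes this choice in its current text, and the wording foresees that the drug received may not be the drug assigned. A route for such an error exists. Active and placebo capsules look identical, site pharmacists are blinded, and dispensing follows bottle or kit numbers. A wrong kit could run for the full 16 weeks, and a single wrong supply for one dispensing period.

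What is at stake is the accuracy of the adverse event tables by arm, and mainly of non-serious events, which have little other reporting behind them.

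**Working it through.** **Arm size.** Section 11.6 asks for 60 per arm (40 m difference, SD 67 m, 90% power, two-sided 0.05). A two-sample t-test calculation gives 59.94, which rounds up to 60. Adding 10% gives 60 × 1.10 = 66 per arm, 132 in total, as stated. This figure only supplies the denominator below.

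**Inputs.**
- 66 subjects per arm (section 11.6).
- Headache 16% on sildenafil and 4% on placebo (Table 8). These come from as-needed use in a different population, so their use here is an assumption.
- Number of placebo-randomised subjects given sildenafil, k: not given in the protocol. Results are shown for k = 1, then for an assumed range up to 5.

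**One error lasting all 16 weeks.** The as-randomised placebo rate is (65 × 4% + 1 × 16%) / 66 = 4.18%. The difference falls from 12.00 to 11.82 points, a loss of 12/66 = 0.18 points.

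**One error lasting part of the time.** Assume a constant hazard and let f be the fraction of the 16 weeks on the wrong drug. The subject's risk is 1 − 0.84^f × 0.96^(1−f), and the loss is (risk − 4%)/66.

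| Weeks on wrong drug | Risk | Loss in difference (points) |
|---|---|---|
| 4 | 7.15% | 0.05 |
| 6 | 8.69% | 0.07 |
| 10 | 11.69% | 0.12 |
| 12 | 13.15% | 0.14 |
| 16 | 16.00% | 0.18 |

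**Several full-length errors.** The difference as randomised is 0.16 − [(66 − k) × 0.04 + k × 0.16]/66. This gives 11.6 points for k = 2, 11.5 for k = 3 and 11.1 for k = 5. With k = 0 the two labellings are identical.

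**Effect on the between-arm test.** More than 10% of 132 means at least 14 subjects with the event. At these rates that happens with probability 45.0%. The table comes from exact enumeration of an unstratified two-sided Fisher test with sildenafil higher. Section 11.3 names a stratified Cochran-Mantel-Haenszel test first, so this is an approximation.

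| Situation | P(p < 0.05) | P(test run and p < 0.05) |
|---|---|---|
| No error (66 v 66) | 54.2% | 31.0% |
| One full-length error, as randomised (66 v 66) | 52.3% | 30.8% |
| Same error, by drug received (67 v 65) | 56.4% | 32.9% |

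The last row cannot be read as a gain, because relabelling one subject cannot do better than having had no error. It reflects the discreteness of Fisher's test. With the same rates and no error at all, P(p < 0.05) is 54.2% at 66 v 66, 56.4% at 67 v 65, 58.7% at 68 v 64 and 62.1% at 65 v 67. A normal approximation, which is smooth, gives 63.5% with no error, 61.8% as randomised and 63.2% by drug received. On that scale one full-length error costs about 1.7 points, and relabelling recovers about 1.4.

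**The case against.** The strongest reply is that nothing in the protocol makes the problem likely. Kit numbers come from a central system, and drug accountability is continuous and checked by the clinical research associate (section 4.4.2.4). Other safeguards do not depend on the tables by arm. Serious events are described in detail (11.3), and unexpected serious events and serious bleeding are all alerted to the DSMB (Table 12). The safety p-values carry no formal weight: "other reported p-values will be considered descriptive" (11.5.3). All of this stands. It limits the size of the point but does not make as-randomised labelling the right choice for safety.

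A reader might infer three stronger things that the protocol does not support.

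- **A clear gain in the chance of detecting harm, from 30.8% to 32.9%.** That contrast is an artefact of discreteness, as shown in the working.
- **A rare harm hidden by one case.** Eight events against none by drug received (67 v 65) gives p = 0.006, while 7 against 1 as randomised (66 v 66) gives p = 0.062. But 8 of 132 is 6.1%, below the 10% threshold, so section 11.3 would not test it. The example also requires the one misdosed subject to be the one with the event.
- **DSMB alerts that are diluted in the same way.** The alert tables in 13.8.1 refer only to treatment and do not name the ITT/Safety set. They say "The counting units are subjects, not events", which fixes the counting unit and not the label. As-randomised labelling there would be an inference.

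Subjects who were randomised but never dosed are a separate question, which this point does not rest on.

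**Conclusion.** The point holds as a minor one. Sections 11.1 and 11.3 together state a rule that, for safety, biases the comparison toward no difference whenever a placebo-randomised subject receives sildenafil. At the assumed headache rates the cost is at most 0.18 points of a 12-point difference per misdispensed subject, and 0.05 to 0.14 points for errors of 4 to 12 weeks. It is zero if no error occurs. These figures rest on borrowed Table 8 rates, a constant hazard for partial exposure, and an error count that the protocol does not give. No study conclusion is shown to change. The case for acting is that the direction is wrong for safety and the change costs very little, so the sponsor could reasonably make it.

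**What to change.** In sections 11.1 and 11.3:

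- Analyse safety by the double-blind study drug actually received. Do not count the open 60 mg sildenafil dose at the baseline catheterisation (Table 2), which subjects later randomised to placebo also take.
- Keep the as-randomised ITT population for efficacy.
- List every subject who received a drug other than the one assigned, with event dates and the drug being taken at the time.
- If any subject differs, also show the as-randomised adverse event table.

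The listing matters most for mixed exposure. A rule that places a subject by the majority of treatment days would leave a completer's single-period error (4/16 = 25% or 6/16 = 37.5% of the time) in the randomised arm. It could also move an event that occurred on the correct drug. How to place such subjects in the tables can be left to the SAP.

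The cost is a few sentences and no new data, since kit numbers and drug use are already recorded. The downside is a slight departure from the randomised comparison for safety, which the as-randomised table covers.
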